### Data Analysis Plan

2.8

To evaluate the feasibility of the ROOTS program (Aim 1), we will use a combination of descriptive statistics and qualitative methods. Descriptive analyses will report progression criteria, including recruitment, enrollment, attendance, and completion rates. We will also compute means, standard deviations, and response distributions on quantitative implementation measures, such as the acceptability of intervention measure (AIM), feasibility of intervention measure (FIM), and intervention appropriateness measure (IAM). To further assess implementation outcomes, we will analyze qualitative interviews from parents and interventionists using thematic analysis (e.g., Braun and Clarke 2006). These interviews will be independently coded by multiple members of the study team using the CFIR framework to identify salient barriers and facilitators across domains (e.g., intervention characteristics, inner and outer settings). We will also map emergent findings onto RE‐AIM dimensions (e.g., adoption, implementation, and maintenance) to assess feasibility and inform potential for scale‐up. Following independent coding, the team will engage in a structured consensus process to resolve discrepancies and refine themes. Final themes will be retained only if they (a) appear across multiple interviews and (b) are independently identified by all coders and agreed upon through consensus discussion.

Preliminary tests of ROOTS' effects (i.e., Aim 2) will be conducted using multilevel modeling (MLM; Fitzmaurice et al. 2011) to account for repeated measures nested within participants in R (R Core Team 2024). Separate mixed effects models will be estimated for each outcome: child social‐emotional functioning, child sleep, physical activity, and sedentary behavior, and parenting variables. Each model will include fixed effects for time (T1, T2, and T3), group (ROOTS vs. control), and the time × group interaction, with child age, gender, and various socioeconomic factors as covariates. All models will follow an intent‐to‐treat (ITT) design, including all randomized participants regardless of intervention completion (Hollis and Campbell 1999). Because this is a pilot study, emphasis will be placed on estimating effect sizes and 95% confidence intervals rather than formal hypothesis testing, consistent with best practices for early‐phase research (Thabane et al. 2010).

Accelerometer data will be downloaded and processed using the GGIR package in R (Van Hees et al. 2015). For sleep, we will use the L512 algorithm to estimate the primary sleep period and extract average nightly sleep duration and quality (e.g., wake after sleep onset). For physical activity, we will calculate daily time spent in sedentary, light, and moderate‐to‐vigorous intensity categories using preschool‐specific cut‐points validated for axivity devices (Migueles et al. 2019; Roscoe et al. 2017). Values will be averaged across all valid days at each timepoint. Finally, for descriptive purposes, we will conduct subgroup analyses based on delivery language (English vs. Spanish) and participant ethnic‐racial background (Latiné vs. non‐Latiné Black) by comparing the effect sizes of intervention outcomes across these groups. We will use restricted maximum likelihood (REML) estimation to analyze longitudinal outcomes, as REML provides less biased estimates of variance components than traditional maximum likelihood, particularly in models with small to moderate sample sizes and repeated measures. REML is well‐suited for linear mixed‐effects models because it accounts for the loss of degrees of freedom associated with estimating fixed effects, which improves the estimation of random effects and yields more reliable standard errors (McNeish 2017).

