### Current Study Aims

1.3

The proposed study involves the development and preliminary evaluation of an integrated family‐based intervention (hereafter referred to as the ROOTS program) to promote the social‐emotional functioning and healthy lifestyle behaviors of Black and Latiné children ages 3–6. This hybrid effectiveness‐implementation study has the following aims: examine various implementation outcomes, such as the feasibility and acceptability of recruitment, retention, and fidelity, as well as potential barriers and facilitators to intervention delivery (Aim 1) and evaluate the pre‐post changes in child and parent outcomes as compared to an active control condition (Aim 2). If successful, this study can provide justification for larger efficacy trials that could ultimately lead to the availability of more holistic integrated interventions for promoting the health and well‐being of Black and Latiné children.

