### Participants

2.2

Eligible parents must (a) live in South Carolina, (b) be able to speak English or Spanish, (c) have access to a device to be able to attend Zoom video calls, and (d) must not have received any parent training services or health services aimed at improving their children's behaviors or lifestyle habits, such as sleep or physical activity promotion programs, in the 12 months before enrolling in the study. Parents must also be the primary caregivers of a child that (e) is between 3 and 6 years of age, (f) is Black/African American or Latiné/Hispanic, and (g) their child must not have any psychological or chronic health issues that significantly interfere with their communication (e.g., child does not understand basic instructions from their parent) or that limit their ability to engage in physical activity (e.g., child uses a wheelchair). Primary caregiver refers to a parent who resides in the same household as the child for at least 50% of the time and has primary custody of the child. We chose to include children with physical or mental health diagnoses as long as these issues did not interfere with key intervention targets, such as their ability to benefit from parenting strategies and adjust their lifestyle behaviors (e.g., physical activity level). These criteria were selected because they align with our universal prevention approach that targets families across the risk spectrum. Target recruitment for this study is 60 families (*n* = 30 experimental, *n* = 30 control).

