### Recruitment and Randomization

2.3

Participants will be recruited using a multifaceted strategy. This involves distributing flyers via email to community partners and displaying them at various locations like schools, daycares, churches, grocery stores, and health clinics. We will also participate in community events, such as back‐to‐school gatherings. To further assist with recruitment, we will hire three designated recruiters who are well‐connected in the community and have experience as community health workers. These recruiters will also act as interventionists (also referred to as parent coaches) for our study. Interested parents can express their interest by calling our designated study phone number, sending an email, or completing an online eligibility form by scanning the QR code shown on the study flyer. After that, research assistants from the ROOTS team will confirm their eligibility during a screening call. Informed consent will be gathered through this screening call and by reviewing qualtrics online forms. Black and Latiné participants will be randomized separately to ensure adequate representation of each ethnic‐racial group within each treatment condition (participants of AfroLatiné descent will be randomized based on language preference). To create each randomization scheme, we will use Excel's random number generator function to produce and save 30 random numbers. These assignments will be hidden in Excel to prevent access by research staff making screening calls. After consenting to participate and completing the T1 assessment, participants will receive a study ID number. This ID number will be added to the appropriate randomization scheme (either Black or Latiné) in the order of enrollment. The random assignment will then be revealed by a designated study staff member.

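### The outcome model gives each arm its own T1 mean, which is valid but yields wider effect intervals than a model that uses the pre-randomisation T1 value

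*Protocol article*

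**What the plan says.** Section 2.8 fixes the mean structure of every outcome model: "Each model will include fixed effects for time (T1, T2, and T3), group (ROOTS vs. control), and the time" by group interaction, "with child age, gender, and various socioeconomic factors as covariates". Estimation is by REML, with repeated measures nested within participants. The outcome at T1 is a response in the model. It is not an adjustment covariate, and nothing sets the T1 means of the arms equal.

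Aim 2 (section 1.3) concerns pre-post "changes in child and parent outcomes as compared to an active control condition". On the reporting of results, section 2.8 says that "emphasis will be placed on estimating effect sizes and 95% confidence intervals rather than formal hypothesis testing".

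On timing, section 2.3 says: "After consenting to participate and completing the T1 assessment, participants will receive a study ID number". The ID is then entered on the randomisation list, and "The random assignment will then be revealed by a designated study staff member". Black and Latiné "participants will be randomized separately to ensure adequate representation of each" group. Section 2.2 adds: "Target recruitment for this study is 60 families", 30 per arm.

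**The concern.** T1 is measured before the arm is known, so within each randomisation stratum the two arms have the same expected T1 mean. The group main effect estimates a difference that the design already sets to zero. The interaction contrast then subtracts the observed T1 difference in full. Conditioning on T1 subtracts only the fraction that predicts follow-up, which removes noise.

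The listed covariates do not recover this loss. Child age, gender and socioeconomic factors, entered as time-constant main effects, cancel from the time by group contrast when data are complete.

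What is at stake is precision. The plan names effect sizes with 95% intervals as the product of Aim 2, and there are only 60 families to produce them.

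**Working it through.** **Inputs from the protocol.** 30 per arm (sections 2.1 and 2.2); three visits; 95% intervals (section 2.8); the progression criterion of at least 60% completing all three assessments (section 2.5.1), which is 18 of 30 per arm.

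**Assumed.** The outcome is in SD units with equal variance and equal correlation rho across visits. Rho is not given, so it is ranged from 0.3 to 0.9. The protocol states no power, SD or interval width, so it has no figure to reproduce.

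**Formulas.** Let N = 30 be the number per arm with T1 and m the number per arm followed at both T2 and T3; the rest have T1 only. For the T2 or T3 effect:

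- Planned interaction contrast: Var = 2[(1 − rho²)/m + (1 − rho)²/N]. With m = N this is 4(1 − rho)/N.
- Common T1 mean: Var = 2(1 − rho²)/m.

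The term 2(1 − rho)²/N is the price of the free T1 means. With complete data the variance ratio is (1 + rho)/2.

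**Example, rho 0.5, complete data.** Planned: 4 × 0.5/30 = 0.0667, SE 0.258, half-width 1.96 × 0.258 = 0.506. Common T1 mean: 2 × 0.75/30 = 0.05, SE 0.224, half-width 0.438. This is 13.4% narrower.

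**Example, rho 0.5, m = 18.** Planned: 2[0.75/18 + 0.25/30] = 0.100, SE 0.316, half-width 0.620. Common T1 mean: 2 × 0.75/18 = 0.0833, SE 0.289, half-width 0.566. This is 8.7% narrower.

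| rho | Complete: planned → common T1 | Narrower | 18 of 30 followed: planned → common T1 | Narrower |
|---|---|---|---|---|
| 0.3 | 0.599 → 0.483 | 19.4% | 0.717 → 0.623 | 13.1% |
| 0.5 | 0.506 → 0.438 | 13.4% | 0.620 → 0.566 | 8.7% |
| 0.7 | 0.392 → 0.361 | 7.8% | 0.491 → 0.467 | 4.9% |
| 0.9 | 0.226 → 0.221 | 2.5% | 0.289 → 0.285 | 1.5% |

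(95% half-widths in SD units.)

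**Simulation, equal variances.** 3,000 trials per rho, with a random intercept fitted by REML. Bias did not differ between the models. Coverage was 0.949 to 0.959 for the planned model and 0.952 to 0.955 for the constrained one.

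**Unequal variances.** For SDs s1 at T1 and s2 at follow-up, with complete data, the planned variance exceeds the conditional one by (2/N)(s1 − rho·s2)², which equals (2/N)·s1²(1 − slope)², where slope = rho·s2/s1. The gain vanishes at slope 1. With s2/s1 = 1.3, the slope is 0.78 at rho 0.6 and 1.04 at rho 0.8.

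In these two cases I compared a constrained model that had only a random intercept with the planned model (2,000 trials each):

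- rho 0.6: true SE 0.271 against 0.275, coverage 0.937 against 0.954.
- rho 0.8: true SE 0.209 against 0.200, coverage 0.925 against 0.954.

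With an unstructured covariance, constrained coverage was 0.945 to 0.957 in all five cases simulated, these two included. The precision gain in these two was negligible.

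**The case against.** The strongest reply is that nothing here is an error. The planned model is standard, unbiased and nominal in coverage, and its interaction contrast matches the wording of Aim 2. That stands: the choice is between two valid estimators. Progression also rests on recruitment, enrolment, session and assessment completion, so no stated decision turns on the width of an effect interval.

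Four stronger readings are tempting, and the documents do not support them.

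- **That every interval narrows at no cost.** A T2-to-T3 contrast gains nothing with complete data. Dropping the group effect while keeping only a random intercept can under-cover, as shown above, where the planned contrast does not.
- **That the plan over-corrects chance imbalance and is therefore biased.** Over-correction holds only conditional on an observed T1 imbalance. Over randomisation the estimate is unbiased.
- **That the planned covariates do nothing.** They cancel only with complete data. With 18 of 30 per arm followed, rho 0.5 and a covariate R² of 0.4 (both assumed), they reduce the planned SE from 0.316 to 0.305.
- **That the fix is worth 20 extra families.** At rho 0.5 it does equal 30/0.75 = 40 per arm, but only with complete data and at that assumed value.

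Section 2.8 also does not name the contrast to be reported. If the arm difference at T2 were read from the planned model instead, then before covariates its half-width would be 1.96 × √(2/30) = 0.506 at any rho. The constrained model is no wider than that either: its ratio to this width is √(1 − rho²), or 0.954 at rho 0.3.

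**Conclusion.** The point holds as a loss of precision. The plan leaves unused information that it has already collected before assignment, and interval width is what Aim 2 is meant to deliver. The likely gain is modest: roughly 8% to 19% for rho between 0.3 and 0.7 with complete data, and 5% to 13% at 60% follow-up. It falls to 2.5% and 1.5% at rho 0.9.

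These figures rest on an assumed rho, equal variances and effects measured from T1. They also take the T1 assessment that section 2.3 places before assignment to include the week of accelerometer wear. Where the slope of follow-up on T1 is near 1, there is almost nothing to gain. The change is worth making because it is cheap and, with an adequate covariance, nothing material is lost.

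**What to change.** Restate the model in section 2.8 as a constrained longitudinal model:

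- categorical time, with group by T2 and group by T3 terms and no group effect at T1;
- an unstructured within-child covariance, not a random intercept alone;
- a term for the ethnic-racial randomisation stratum, so that the common T1 mean applies within stratum;
- the covariates already listed.

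Keep all randomised families with T1 data in the model, including those with no follow-up, so that the intention-to-treat statement still holds.

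The alternative is to model T2 and T3 with the T1 outcome as a covariate. At 30 per arm, estimating that slope costs a variance factor of 1 + 1/(60 − 4) = 1.018, so with equal variances it beats the change contrast up to rho of about 2/1.018 − 1 = 0.96.

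The cost is a slightly richer covariance model and a change of wording and code. No new data are needed. The change should be recorded before outcomes are analysed by arm.

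### Randomisation runs on separate Black and Latiné lists, but the list is not among the covariates stated for the outcome models, and the ethnic-racial subgroup classes AfroLatiné families differently

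*Protocol article*

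**What the plan says.** Recruitment and Randomization (2.3) stratifies allocation: "Black and Latiné participants will be randomized separately to ensure adequate representation of each ethnic‐racial group within each treatment condition". For families who belong to both groups, "participants of AfroLatiné descent will be randomized based on language preference". Each scheme is built the same way: "we will use Excel's random number generator function to produce and save 30 random numbers". At assignment, "This ID number will be added to the appropriate randomization scheme (either Black or Latiné) in the order of enrollment". The article mentions no blocking or other restriction.

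The Data Analysis Plan (2.8) sets out one model form for all outcomes: fixed effects for time, group and time × group, "with child age, gender, and various socioeconomic factors as covariates". Neither the list nor race/ethnicity nor language is named.

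Demographics and Other Covariates (2.5.4) collects race/ethnicity and preferred language at T1. It says that such factors will be examined as possible covariates or moderators, without committing to any of them.

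The Data Analysis Plan also describes subgroup analyses, labelled descriptive, by delivery language and by ethnic-racial background (Latiné against non-Latiné Black), carried out "by comparing the effect sizes of intervention outcomes across these groups".

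**The concern.** The list is the only factor on which randomisation is stratified, and it was chosen so that both groups would be represented in both arms. The analysis section states what each model contains and leaves it out. If the two lists are unrestricted, the arms can still differ by chance in their mix of Black and Latiné families, and the stated model does not adjust for that. The article makes effect sizes and 95% confidence intervals its main Aim 2 output, so an avoidable chance shift in those estimates is worth removing.

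The second issue is one of definition. Section 2.3 assigns AfroLatiné families to a list by language preference. The subgroup split in section 2.8 puts every AfroLatiné family under Latiné. A family on the Black list could therefore be analysed as Latiné.

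**Working it through.** **Inputs from the article.** Two lists of 30 random numbers; 60 families; 30 per arm; 1:1 ratio; three assessments; mixed models with time × group, fitted by REML. The lists and the target agree: 2 × 30 = 60 = 30 + 30. The article gives no SD, effect size, dropout rate, list effect or AfroLatiné share, so those below are assumptions.

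**1. Can the arms be unbalanced by list?** If each number independently decides the arm, the count in one arm of a list is binomial(30, 0.5).
- P(exactly 15/15 in a list) = 14.4%. For both lists, 0.1445² = 2.1%.
- P(a given list splits 18/12 or worse) = 36.2%. For at least one list, 1 − (1 − 0.3616)² = 59%.
- P(the arms differ by 20 points or more in their share of Black families) = 15.5%, by summing over both lists.

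If the full protocol restricts the lists to 15/15, these probabilities do not apply to full lists. The article does not say which holds.

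**2. What does imbalance do to the effect on change?** Shift = (difference between arms in share of Black families) × (difference between lists in mean change). With a 20-point difference and an assumed list difference of 0.3 to 0.5 SD:
- 0.20 × 0.3 = 0.06 SD
- 0.20 × 0.5 = 0.10 SD

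Against a standard error of 0.2605 SD (step 3), this is 0.06/0.2605 = 0.23 to 0.10/0.2605 = 0.38 of a standard error.

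**3. Which model term corrects it?** With complete data, time × group is a contrast within families. A list main effect adds the same amount to all three of a family's values and cancels. Only list × time can act on the contrast. Simulation agrees: 60 datasets per setting, random-intercept REML, unrestricted allocation, list explaining 20% of outcome variance (assumed) but not affecting change. Results are for the T2 × group term, in SD units.

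| Model | Mean SE, complete data | Mean SE, 20% of follow-up missing (assumed) |
|---|---|---|
| No list | 0.2605 | 0.2783 |
| List main effect | 0.2605 | 0.2773 |
| List and list × time | 0.2625 | 0.2799 |

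Adding the main effect changed the estimate by 0.0 with complete data and by at most 0.086 SD with 20% missing. With list × time, the price when list does not predict change is 0.2625/0.2605 = 1.008, about 0.8% on the standard error with complete data. The extra parameters are 1 for list and 2 for list × time, so 3.

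**4. How many families are classed differently?** Assume that English-preferring AfroLatiné families go to the Black list, which the text implies but does not state. Families affected = 60 × AfroLatiné share × share preferring English.
- Low: 60 × 0.02 × 0.5 = 0.6
- High: 60 × 0.10 × 1.0 = 6

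That is about 1 to 6 families, or 2% to 20% of a Black list of 30. For all other families, list and subgroup coincide.

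**The case against.** The strongest reply is that race/ethnicity is not excluded: section 2.5.4 keeps it as a potential covariate, and a condensed article may leave the exact covariate set to a fuller document. This stands in part. The fair description is that the list is not prespecified, rather than ruled out. But section 2.8 does state what each model includes, a potential covariate is not a commitment, and race/ethnicity is not the same variable as the list for AfroLatiné families.

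A second reply is that the size is small, and that stands. The shift in step 2 is chance imbalance with expectation zero over randomisation. It needs unrestricted lists, an uncommon imbalance and an assumed list effect on change. The progression criteria rest on recruitment, enrolment, session completion and assessment completion, so none depends on this covariate.

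Three stronger readings are tempting, and the documents support none of them.
- **The planned confidence intervals are wrong without the list.** Simulated intervals were too wide (coverage 96.2% to 98.3% when list explains 10% to 30% of variance) only for a single-timepoint comparison with lists fixed at 15/15. The article does not plan that analysis, and the error is conservative. With unrestricted lists, coverage of that comparison was about 95% with or without the list.
- **The subgroups lose their randomised comparison.** Ethnic-racial background is a baseline trait, so arms within each subgroup are still compared as randomised. A subgroup need not equal a stratum.
- **Delivery language is chosen after allocation.** No text says so. Program Format and Delivery (2.4.3) ties session language to the parent's preference, and preferred language is recorded at T1.

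**Conclusion.** The point holds as a modest mismatch between design and analysis. Allocation is stratified by list, the models as stated do not include it, and the possible use of race/ethnicity does not close the gap. The likely size is 0.06 to 0.10 SD in an unfavourable allocation. This rests on unrestricted lists, a 20-point imbalance and an assumed list difference in change of 0.3 to 0.5 SD. If the lists are held at 15/15, or if list does not predict change, little would alter in the planned contrast. The two classifications of AfroLatiné families are a real inconsistency, but a minor one: about 1 to 6 of 60 families under assumed shares, in an analysis that is descriptive only.

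**What to change.** In the Data Analysis Plan, name the randomisation list (the one actually used for each family) as a prespecified fixed effect in every outcome model, together with list × time. Then either define the ethnic-racial subgroup by that list, or state in both sections how AfroLatiné families are classed and why the two rules differ. It would help to say which language preference leads to which list.

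The cost is wording and code, about three degrees of freedom, and a standard error roughly 0.8% larger if list turns out not to predict change. No new data are needed, because the list is recorded at assignment.

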## Abstract

**Trial Registration:**

The trial began recruiting in May 2024 (Trial Registry: NCT06111651, Version 5, June 13, 2024). Participants are expected to complete their 3‐month follow‐up assessments at the end of fall 2025.

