### Study Setting and Design

2.1

Because the protocol will be implemented virtually, families living anywhere in the state of South Carolina will be able to participate. To pilot the feasibility of the ROOTS program, the study will use a longitudinal two‐arm randomized control trial design in which families are randomized into a parenting intervention (*n* = 30) or a control (*n* = 30) condition on a 1:1 ratio. We selected a nutrition control condition that is a similar length (6 weeks) and provides a similar structure (offers parents new strategies and a workbook to reflect on their progress and goals). This decision was based on empirical evidence suggesting a need for alternative approaches to intervention research to maximize participant engagement and minimize ethical concerns related to withholding services from underserved populations (Henry et al. 2017). Assessments will occur at three timepoints: pre‐intervention (T1), post‐intervention (T2), and 3‐month follow‐up (T3). After completing the third assessment, each condition will have the opportunity to receive the materials from the other condition.

The hybrid effectiveness‐implementation approach adopted for this study examines intervention outcomes while concurrently assessing barriers and facilitators related to successful program delivery (see Figure 1). Blinding will occur at several levels, primarily with participants, outcome assessors, and data analysts. For example, intervention participants will not be aware of which intervention group is considered the treatment or control; rather, they will be instructed that the study seeks to compare the effects of two health interventions. Outcome assessment will be conducted using Qualtrics, which prevents potential bias from using unblinded assessors. Blinding will also occur at the data analyst level, specifically related to assessing outcomes.

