#### Intervention Outcomes

2.5.3

To assess preliminary intervention effects, this study will use a combination of validated parent‐report scales and objective measures to evaluate child and parent outcomes across three timepoints (T1–T3). Main child outcomes include social‐emotional functioning, sleep, physical activity, and sedentary behavior. Social‐emotional functioning will be measured using the strengths and difficulties questionnaire (Goodman 1997). Sleep, physical activity, and sedentary behavior will be measured using axivity accelerometers worn on the nondominant wrist for 7 consecutive days. Sleep variables (e.g., duration, quality) and physical activity variables (e.g., average minutes of sedentary, light, and moderate physical activity) will be derived using validated algorithms, such as the L512 algorithm within GGIR; Van Hees et al. 2015), and using age‐appropriate cut‐points (Migueles et al. 2019). We will assess the acceptability of the accelerometers by evaluating the number of full days (or nights) of wear data provided by each child. Secondary parenting outcomes will include parenting practices, ethnic‐racial socialization behaviors and attitudes, and parenting self‐efficacy. Each measure is described in Table 3, including psychometric properties and language validation status (English and/or Spanish). Measures not available in Spanish (i.e., parent–child sleep interactions scale, racial socialization competency scale) will be translated by bilingual study team members or a professional service using recommended procedures. This includes forward and back‐translation, reconciliation of discrepancies, and pilot testing to ensure cultural and linguistic appropriateness. This pilot study will also serve as an opportunity to examine the reliability and validity of these translated measures within our Spanish‐speaking sample.

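### The accelerometer models have no calendar term, so season and school breaks add avoidable variance to the arm contrast and can confound within-arm change

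*Protocol article*

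**What the plan says.** Three of the four main child outcomes are accelerometer measures. Under Intervention Outcomes the device is "worn on the nondominant wrist for 7 consecutive days", once at each of T1, T2 and T3. The Data Analysis Plan then says "Values will be averaged across all valid days at each timepoint".

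The same section lists the model: "Each model will include fixed effects for time (T1, T2, and T3), group (ROOTS vs. control"), their interaction, "with child age, gender, and various socioeconomic factors as covariates". No listed term depends on the calendar date of measurement.

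On timing, the registration paragraph says "The trial began recruiting in May 2024" and expects the 3-month follow-ups to finish at the end of fall 2025. The recruitment benchmark under Feasibility and Implementation Outcomes is 60 families in 12 months. "Target recruitment for this study is 60 families", split 30 and 30. Aim 2 evaluates pre-post change "as compared to an active control condition (Aim 2").

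**The concern.** Sleep, activity and sedentary time in 3–6-year-olds plausibly follow the season and the school or childcare calendar. With enrolment spread over about a year, T1 is a summer-break week for one child and a school week for another, and many children cross a break between timepoints. The T1/T2/T3 factor takes out only the average shift at each visit. It cannot take out a calendar effect that falls on different visits for different families.

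Two things are at stake. The pilot's stated product for Aim 2 is effect sizes with 95% confidence intervals, and unexplained calendar variation widens those intervals in a sample of 60. Separately, anyone who reads the change within the ROOTS arm alone may be reading a seasonal drift.

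**Working it through.** The article gives no power calculation and no seasonal or weekday figure, so there is no stated number to reproduce.

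**1. Enrolment window.** Recruitment starts in May 2024. Taking T3 at about 19 weeks after T1 (6 weeks of programme plus 13, assumed) and the end of fall as 30 November to 21 December 2025, the last T1 falls between 20 July and 10 August 2025. From mid-May 2024 that is about 14–15 months, so enrolment of roughly a year fits the article.

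**2. How many children change school status.** Assumptions: uniform enrolment over 365 days from 15 May 2024; T2 at 49, 56 or 63 days; T3 at 140, 147 or 154 days; school out 1 June–10 August and 21 December–3 January. Counting enrolment days on which status differs:

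| Interval | Days that switch, of 365 | Share |
|---|---|---|
| T1–T2 | 126, 140, 154 | 35%, 38%, 42% |
| T1–T3 | 154, 142, 130 | 42%, 39%, 36% |

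Under uniform enrolment the mean change in status is 0, so its variance *v* equals the share: 0.345 to 0.422.

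**3. Effect on the standard error.** With outcome SD 1, within-child correlation *r* and school-out effect *e*, the variance of a child's change is 2(1 − r) + e²v. The SE of the arm difference is multiplied by √[(2(1 − r) + e²v) / (2(1 − r))].

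- Smallest case, r = 0.5, v = 0.345: e = 0.3 gives √1.031 = 1.015; e = 0.5 gives √1.086 = 1.042; e = 0.8 gives √1.221 = 1.105.
- Largest case, r = 0.6, v = 0.422: e = 0.3 gives √1.047 = 1.023; e = 0.5 gives √1.132 = 1.064; e = 0.8 gives √1.338 = 1.157.

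The increase is therefore about 2%, 4–6% and 10–16%.

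**4. The same quantity as chance imbalance.** One SD of the shift from unequal calendar mix between arms is e√v√(2/30), about 0.05, 0.08 and 0.13 SD. This is not an extra cost. At r = 0.5 the SE without a calendar effect is √(2/30) = 0.258. Adding 0.050 in quadrature gives 0.263, or 1.019 times, which is the inflation in step 3 for e = 0.3 and v = 0.422.

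**5. A different seasonal shape.** With a sinusoid of amplitude A, uniform 52-week enrolment and r = 0.5, the added variance of change is 2A² sin²(π × gap/52). For the 19-week gap and A = 0.2, 0.3, 0.5 this is 0.067, 0.150 and 0.416, so the SE is 1.03, 1.07 and 1.19 times its no-season value. For a 6-week gap the multipliers are 1.005, 1.01 and 1.03.

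**6. Bias or noise.** In 20,000 simulated trials per setting (30 per arm, equal visit timing in both arms, enrolment over 12, 26, 52 or 65 weeks), the mean arm contrast was within 0.006 SD of 0 and 95% interval coverage was 94.8–95.3%. The within-arm T1–T3 change behaved differently. At A = 0.3 its mean was about 0.00 SD with 52-week enrolment, −0.09 with 65 weeks, −0.14 with 26 weeks and −0.48 with 12 weeks.

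**7. Weekday mix.** Complete wear over 7 consecutive days contains 5 weekdays and 2 weekend days, so the plain mean equals a 5:2 weighted mean. For incomplete wear, one child's error is D × (weekend share − 2/7). With an assumed weekend–weekday gap of D = 45 min, no weekend day gives −13 min, and two weekdays plus two weekend days give +10 min. At trial level, with days lost at random and D of 0.3–1.0 SD, the mean shift is about 0 and the SE rises by 0.1–3%.

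**The case against.** Three stronger readings are tempting, and the article supports none of them.

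*Season is mistaken for a treatment effect.* Under Recruitment and Randomization, T1 is completed before allocation is revealed, so its date cannot depend on arm, and the control is concurrent. Season then cancels in expectation from the time × group term, and the confidence interval already carries the remaining noise. Year-round enrolment also helps: it averages season out of the time effect, whereas short or clustered enrolment confounds it (step 6).

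*Averaging over valid days biases the comparison.* That would need weekend wear to be lost differently by arm, which nothing in the article indicates. One weekend day lost per child in one arm only would move the contrast by D × (2/7 − 1/6), that is 0.04, 0.06 or 0.12 SD for D = 0.3, 0.5 or 1.0 SD. Replacing the plain mean with a 5:2 weighted one is no clear gain either. With days lost at random, simulation shows that weighting raises error unless the weekend–weekday gap exceeds about one day-to-day SD.

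*T2 drifts later in ROOTS because its sessions are attended and the control is self-directed.* No text says T2 waits for the sixth session. Both programmes are described as six weeks or similar, Data Collection encourages families who leave the intervention to stay in assessments, and the schedule is in Figure 1, which is not shown here. A material bias would need both a ROOTS-only delay and clustered enrolment: a four-week delay with enrolment bunched in four months changes the share of T2 weeks out of school by 23 percentage points, about 0.12 SD at an assumed 0.5 SD effect. The article establishes neither condition.

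It is also fair to say that valid-day rules may sit in an analysis plan not seen here, that the 12-month figure is a progression benchmark and not an enrolment schedule, and that the article does not say which children attend school or childcare. All of this stands, and it limits the point to an improvement on the model as stated.

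**Conclusion.** The point holds as a modest matter of precision, together with a caution about interpretation. The stated covariates omit a source of variation that can be read off the wear date. Leaving it out costs about 2% to 16% in the SE of the arm difference in change, for assumed school-out effects of 0.3 to 0.8 SD and within-child correlation of 0.5–0.6. This is the most an adjustment could recover, since it assumes that the term captures the whole calendar effect. If children's behaviour barely follows the school calendar, the gain is close to nil. The expected time × group contrast is the same with or without the term. The T1–T3 change within a single arm can be off by a tenth of an SD or more when enrolment is uneven (A = 0.3, 26 weeks or less).

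**What to change.** Add to each accelerometer model one time-varying, two-level term set by the date of the wear week: school in session versus break according to a named calendar, or season. Fix its definition before the outcome data are analysed by arm. State that effects will be read from the time × group contrast and that change within an arm will not be interpreted alone.

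Keep the plain mean over valid days as the main summary. A weekday/weekend-weighted mean may be reported as a sensitivity analysis, without excluding children who have no valid weekend day from the main analysis. The timing of T2 and T3 needs no change on this account.

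The cost is one degree of freedom per model and a few lines of analysis text. A finer season coding would cost more degrees of freedom. No new data are needed if the wear dates are kept with the accelerometer files, and the change remains possible with the trial under way.
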